## Abstract

**Background:** Cancer cachexia and exacerbated fatigue represent two hallmarks in cancer patients, negatively impacting their exercise tolerance and ultimately their quality of life. However, the characterization of patients' physical status and exercise tolerance and, most importantly, their evolution throughout cancer treatment may represent the first step in efficiently counteracting their development with prescribed and tailored exercise training. In this context, the aim of the PROTECT-01 study will be to investigate the evolution of physical status, from diagnosis to the end of first-line treatment, of patients with one of the three most common cancers (i.e., lung, breast, and colorectal).

**Methods:** The PROTECT-01 cohort study will include 300 patients equally divided between lung, breast and colorectal cancer. Patients will perform a series of assessments at three visits throughout the treatment: (1) between the date of diagnosis and the start of treatment, (2) 8 weeks after the start of treatment, and (3) after the completion of first-line treatment or at the 6-months mark, whichever occurs first. For each of the three visits, subjective and objective fatigue, maximal voluntary force, body composition, cachexia, physical activity level, quality of life, respiratory function, overall physical performance, and exercise tolerance will be assessed.

**Discussion:** The present study is aimed at identifying the nature and severity of maladaptation related to exercise intolerance in the three most common cancers. Therefore, our results should contribute to the delineation of the needs of each group of patients and to the determination of the most valuable exercise interventions in order to counteract these maladaptations. This descriptive and comprehensive approach is a prerequisite in order to elaborate, through future interventional research projects, tailored exercise strategies to counteract specific symptoms that are potentially cancer type-dependent and, *in fine*, to improve the health and quality of life of cancer patients. Moreover, our concomitant focus on fatigue and cachexia will provide insightful information about two factors that may have substantial interaction but require further investigation.

**Trial registration:** This prospective study has been registered at ClinicalTrials.gov (NCT03956641), May, 2019.

## Introduction

Hallmark symptoms in patients with cancer include exacerbated fatigue (1, 2) and muscle wasting (3, 4) which impair their quality of life (2, 5, 6). Importantly, these are due to both the disease and the antineoplastic treatments (2, 4, 6–8), resulting in substantial differences across cancer types (3, 8–12). The characterization of these key parameters and, most importantly, their evolution throughout cancer treatment may represent the first step in finding ways of efficiently counteracting their development.

Cancer-related fatigue (CRF) is considered the main symptom in cancer patients and can be defined by clinicians as a chronic sensation of tiredness that is not fully reversed by rest, unlike common fatigue experienced by healthy individuals (1, 2), and is assessed subjectively with questionnaires. Moreover, as a multi-factorial symptom, CRF is also documented by objective measurements of neuromuscular fatigue, such as changes in force output (13). Previous studies report that 60–96% of cancer patients experience CRF (14), a symptom that persists even after treatments conclude (8, 15). As a consequence, daily activities are affected (16) and physical activity levels are largely decreased (17, 18), affecting, in turn, skeletal muscle mass and function.

Skeletal muscle plays a major function in daily activity and possesses the ability to adapt according to applied stresses. This characteristic plasticity expresses itself through both structural and metabolic adaptations, and it is well-known that a decrease in muscle activity will lead to muscle deconditioning (19–23). In the context of cancer patients, the combination of a decrease in muscle mass and strength, an increase in fatigue, and a perturbation of identified biomarkers (i.e., inflammation, albumin, and hemoglobin) is known as cachexia (3, 24–26). It is a multifactorial syndrome characterized by ongoing loss of skeletal muscle mass (with or without loss of fat mass) that cannot be fully reversed by conventional nutritional support, leading to progressive functional impairment (4). Cachexia is considered a major public health problem and another important symptom in cancer patients (27). Indeed, a high level of cachexia is known to be associated with poor quality of life (6), reduced survivability (28), and massive public health costs (29). Cachexia also negatively impacts both perceived and/or objective CRF (5, 30–32), thus placing cancer patients in the center of a vicious cycle with fatigue inducing cachexia and cachexia inducing fatigue (Figure 1). This cachexia–fatigue vicious cycle suggests a strong interconnection between CRF and cachexia.

**Figure 1 F1:**
[figure not shown]
Illustration of the theoretical cachexia–fatigue vicious cycle.

Exercise interventions have been investigated for improving CRF in many studies (33), with positive effects and a widespread agreement that they represent some of the most efficient interventions in cancer patients (34, 35). Exercise interventions also appear to be the best interventions to counteract cachexia specifically (36–38). For example, several studies have shown that exercise interventions in cancer patients are able to increase anti-inflammatory cytokine expression (IL-10, IL-15) and therefore decrease systemic pro-inflammatory factors (TNF-α, IL-6) responsible, at least in part, for the unbalanced protein turnover signaling and muscle deconditioning observed in this population (36–38). Today, exercise interventions are increasingly being recognized as an efficient strategy in counteracting both CRF and cachexia in cancer patients. Indeed, the implementation of supportive care with adapted physical activity in cancer patients is part of current and future political recommendations in France (39, 40) and elsewhere (41–43).

However, despite a great number of studies showing the positive effects of exercise interventions on many different health parameters (44–46); the literature also highlights the significant variability of patient adaptation to exercise programs (33, 47, 48). This variability appears to be accountable for the lack of tailored exercise interventions (49) and occurs due to the large number of parameters that influence the effects of exercise prescribed to patients: the type and stage of cancer, the type of treatment, and the physical status at the time of diagnosis. For example, lung cancer patients present a higher risk of cachexia, whereas breast cancer patients present a higher risk of heart failure (9, 50). All these different parameters, and their evolution throughout treatment, should be considered in prescribing the best exercise strategies on an individual basis, as opposed to generic exercise programs.

In this context, the aim of our study will be to describe, in cancer patients, the evolution of their physical status from diagnosis until the end of first-line treatment. This prospective cohort study will include patients with lung, colorectal, and breast cancer as they represent ~30% of all newly diagnosed cancers (51).

## Materials and Methods

### Study Population

As they represent ~30% of all newly diagnosed cancers (51), this cohort study will focus on three different cancer types: breast, lung, and colorectal. The detailed inclusion and exclusion criteria are summarized in Table 1.

**Table 1 T1:** Inclusion and exclusion criteria.

**Inclusion criteria**	**Exclusion criteria**
• First-line cancer treatment	• Psychiatric, musculoskeletal, or neurological disorders
• Breast cancer, Stage II or III, treated by taxane-based CT	• Pregnant or nursing women
• Colorectal cancer, stage IV, treated by CT, RT, IT, or TT	
• Non-small cell lung cancer, stage III or IV, treated by CT, RT, IT, or TT	
• Age ≥18 years	
• Performance status WHO 0–2	
• Life expectancy >6 months	
• Ability to speak, understand and read French	
• No contraindication to physical assessments	
• Affiliate to social security system	
• Give written inform consent	

*CT, chemotherapy; IT, immunotherapy; RT, radiation therapy; TT, targeted therapy; WHO, World Health Organization performance status*.

Patients newly diagnosed with cancer by an oncologist and satisfying inclusion and exclusion criteria described in Table 1 will be informed of the study protocol. If interested, the patient will contact one of the study coordinators for full information about the study as well as to discuss any questions pertaining to it. Once the patient has provided the written consent form to participate in this study, the visits will be scheduled.

### Study Design

This cohort study aims to investigate the evolution of physical status from diagnosis to the end of first-line treatment. Therefore, after signing the written consent form, three visits will be scheduled. All assessments, detailed hereafter, will be performed at inclusion (Visit 1, between the time of diagnosis and the beginning of the treatment), 8 weeks after the beginning of the treatment (Visit 2), and either during the week after completion of first-line treatment or at the 6-months mark (Visit 3), whichever occurs first. The PROTECT-01 enrolment time is 18 months, and the study design is detailed in Figure 2.

**Figure 2 F2:**
[figure not shown]
Flowchart of the PROTECT-01 study design.

### Study Assessments

In order to assess the evolution of our different measurements throughout cancer treatment, all assessments will be performed via the same methods and under the same conditions across the three visits. All of the assessments will be performed chronologically in the order that they appear in the description provided hereafter. All parameters analyzed in this study are displayed in Table 2.

**Table 2 T2:** Study time points.

	**Before the start of treatment**	**8 weeks after the start of treatment**	**End of treatment or 6 months**
	**Visit 1** **1st assessment**	**Visit 2** **2nd assessment**	**Visit 3** **3rd assessment**
Inclusion criteria check-up	X		
Informed consent	X		
**Clinical data**			
Participant information	X		
Disease history	X		
Cancer record	X	X	X
Cancer treatment	X	X	X
Performance status WHO	X	X	X
Concurrent treatments	X	X	X
**Questionnaires**			
FACIT-F	X	X	X
GPAQ	X	X	X
EORTC QLQ-C30	X	X	X
**Physical assessments**			
Body composition	X	X	X
Cachexia		X	X
Respiratory function	X	X	X
Maximal voluntary force	X	X	X
Fatigability	X	X	X
Physical performance	X	X	X
Exercise tolerance	X	X	X

*Visit 1, between the time of diagnosis and the beginning of the treatment; Visit 2, 8 weeks after the beginning of the treatment; Visit 3, at the end of first-line treatment or at the 6-months mark; EORTC QLQ-C30, European Organization for Research and Treatment of Cancer Quality of Life Core Questionnaire; FACIT-F, Functional Assessment of Chronic Illness Therapy–Fatigue; GPAQ, Global Physical Activity Questionnaire; WHO, World Health Organization performance status*.

### Clinical Data

Age, gender, tobacco consumption, significant health history (e.g., disease, surgery), type of cancer, and date of diagnosis will be collected via the medical file at the first visit. The presence of metastases and their sites, type of treatment (chemotherapy, immunotherapy, targeted therapy, radiotherapy) for lung and colorectal cancer patients, disease stage, performance status WHO, and significant concomitant treatments (e.g., corticosteroids, analgesics, antidepressants, antihypertensives) will also be collected and tracked throughout the study.

### Questionnaires

Perceived cancer-related fatigue will be reflected by the score of the Functional Assessment of Chronic Illness Therapy–Fatigue (FACIT-F) scale version 4 (52). The FACIT-F is a subscale of the FACIT scales, a collection of health-related quality of life questionnaires targeted to the management of chronic illness. Patients will answer a 13-item scale to report their fatigue and its impact on their daily life during the previous week. Items are rated on a 0–4 intensity scale (0: not at all, 1: a little bit, 2: somewhat, 3: quite a bit, 4: very much). After performing reversal scores for appropriate items, scores will be analyzed through two specific subscales (health-related quality of life and fatigue) and the global score obtained from the FACIT-F, where higher scores indicate less fatigue or better functioning.

Physical activity level will be assessed using the 16-item Global Physical Activity Questionnaire version 2 (GPAQ-2) (53). GPAQ-2 collects information on sedentary behavior and physical activity in three domains: (1) activity at work, (2) travel to and from places, and (3) recreational activities during a typical week. Patient engagement in moderate and vigorous physical activity level is assessed based on dichotomous response (i.e., “yes” or “no”). Intensity of activities are classified using MET (Metabolic Equivalent of Task) as follows: inactivity (1 MET), moderate (4 METs), and vigorous (8 METs). For patients performing moderate and/or vigorous activities, they will also have to report their frequency (number of days per week) and duration. Then, a score will be calculated based on the characteristics (i.e., MET, frequency, and duration) of activities in the moderate and vigorous domains. The higher the score, the better the patient's physical activity level.

Quality of life will be evaluated by the European Organization for Research and Treatment of Cancer (EORTC) Quality of Life Core Questionnaire (EORTC QLQ-C30), version 3, with 30 items (54). The self-administered EORTC QLQ-C30 is specifically designed for cancer patients, and version 3 is intended for all patients with cancer regardless of tumor site. The questionnaire includes five functioning scales (physical, role, cognitive, emotional, and social functioning) and three symptom scales (fatigue, pain, and nausea/vomiting). Additional cancer symptoms (dyspnea, sleep disturbance, loss of appetite, diarrhea, and constipation) and financial difficulties due to cancer and treatments are also reported by separate items. Patients will score intensity of symptoms during the past week for each item on a scale of 1–4 (1: not at all, 2: a little, 3: quite a bit, 4: very much). Patient overall global health and quality of life will be assessed, ranging from 1 to 7 (1 for very poor to 7 for excellent). A total score between 0 and 100 will be calculated for each scale. For global and functioning scales, a higher score is considered better, while for symptom scales a lower score is better.

### Body Composition and Cachexia

Body mass and composition analyses will be performed using a bioelectrical impedance meter (SECA mBCA 515, SECA, Hamburg, Germany), validated in comparison to different robust methods assessing body composition, such as air-displacement plethysmography, dual-energy X-ray absorptiometry, and deuterium dilution (55). The bioelectrical impedance meter is also regularly used in studies investigating body composition in cancer patients (56–59). We will quantify body mass, fat free mass, fat mass, skeletal muscle mass, visceral fat, and body water repartition. Patient height will be measured to calculate body mass index (BMI, body mass/height^2^).

In accordance with Fearon et al. (4), cachexia will be diagnosed using fat-free mass index cut-off (i.e., <14.6 kg/m^2^ for men and <11.4 kg/m^2^ for women) assessed by a bioelectrical impedance meter (4). Furthermore, the severity of the cancer-related body mass loss (i.e., cachexia) will be investigated using the Martin score (28) at the second and third visit. Martin score is a robust grading system incorporating the independent prognostic significance of both BMI and percentage of body mass loss based on a correlation matrix from a cohort of more than 8,000 cancer patients (28). A severity stage of body mass loss between 0 and 4 is attributed to each patient according to their BMI at cancer diagnosis (28), with stage 0 being the lowest severity stage of cachexia, and stage 4, the highest. Importantly, each score is associated with a specific cumulative survival curve: the lower the score, the greater the survival probability (28).

### Respiratory Function

Respiratory function will be assessed using a portable spirometer (USB Electronique Portable *Spirobank II* Smart MIR, Rome, Italy). Patients will have to take maximum inspiration and blow to maximum exhalation. The mouthpiece on the device will be changed between each patient. The measured parameters will be: forced expiratory volume in the first second (FEV1), forced vital capacity (FVC), Tiffeneau index or FEV1% (FEV1/FVC), peak exploratory flow (PEF), mean forced expiratory flow between 25 and 75% of FVC (FEF 25–75%), inspiratory vital capacity (IVC), expiratory vital capacity (EVC), inspiratory capacity (IC), expiratory reserve volume (ERV), and tidal volume (TV).

### Maximal Voluntary Force

Finger flexors force will be measured using a handgrip dynamometer (Takeï, TK200, Takei Scientific Instruments, Tokyo, Japan). Patients will sit upright in a chair with their feet touching the ground. The dominant arm will be placed with the elbow flexed at 90° on a table, while the forearm and the hand will be placed in a neutral position (Figure 3A). The non-dominant arm will be relaxed in a neutral position. For standardization, grip settings will be set at 5.1 cm (Figure 3A), corresponding to the standard position for grip testing (60, 61). Knee extensors force will be measured with a force transducer (Force sensor kit, Chronojump, Barcelona, Spain) positioned on a leg extension device (ProForma—Bodytone Evolution Extensions, Barcelona, Spain) (Figure 3B). Patients will be assessed in a seated position with the hip and knee joints fixed at 100 and 90°, respectively (where 180° represents a full knee extension), and aligned in the frontal axis. The lower leg will be attached with a non-compliant strap right above the malleoli. All participants will be familiarized with the maximal voluntary isometric contractions until the observation of a force plateau, indicating the ability to maintain the maximal contraction over 3 s and consistent peak values (≤5% difference) between trials. After a standardized warm-up (three contractions at 25, 50, and 75% of the estimated maximal voluntary contraction [MVC] torque), patients will be asked to perform three 3-s maximal voluntary isometric contractions under verbal encouragement. A 30-s rest period will be given between each MVC. The maximal value measured during the three trials will be used for further analysis.

**Figure 3 F3:**
[figure not shown]
Illustration of the neuromuscular assessments. Participant's position for finger flexor **(A)** and knee extensor **(B)** assessments and schematic representation of the protocol **(C)**.

### Fatigability

Patients will be placed in the same position as the maximal voluntary force assessment. For both finger flexors and knee extensors, fatigability will be assessed by performing ten 3-s maximal voluntary isometric contractions under verbal encouragement with a 2-s rest period between each contraction. Fatigability will be calculated as the percent difference in peak force between the first and the last contraction (62).

### Physical Performance

Physical performance will be assessed using the Short Physical Performance Battery (SPPB), a validated and reproducible test (interclass correlation coefficient of 0.86), indicating the risk of skeletal muscle force and mass loss in older adults (i.e., sarcopenia) (19, 63, 64). The SPPB test includes balance tests (joint feet, semi-tandem feet, and tandem feet), a 4-m walking speed test, and a 5-times-sit-to-stand test. For the balance tests, patients will be timed over a 10-s period and stopped if they lose their balance during this time. For the walking speed test, patients will have to walk spontaneously over 4 m, two times, and the fastest trial, in m·s^−1^, will be used for further analysis. For the 5-times-sit-to-stand test, a chair (height, 43–45 cm; depth, 47.5 cm) will be used. With their arms crossed over their chest, patients will have to sit and stand five times as fast as possible on two different trials. Here again, the best performance will be used for analysis.

### Exercise Tolerance

Exercise tolerance will be assessed using the classical 6-min walking test (6-MWT), following the American Thoracic Society (ATS) Statement recommendations (65). The 6-MWT is a validated and reproducible test (interclass correlation coefficient of 0.85), associated with mortality in cancer patients (66, 67). Patients will walk in a covered, flat, straight, well-delineated (marked every 3 m) and with no disturbance, 20-m corridor. A starting line will be marked, and two cones will represent the location of the U-turns. Physiological measurements (mean arterial pressure, oxygen saturation, and heart rate) will be performed at rest, at least 10 min before the beginning of the test, and again immediately at the end of the 6-MWT. Instructions will systematically be given to the patient as recommended in the ATS Statement (65). The total distance covered during the test (in meters) will be used to assess exercise tolerance.

### Sample Size

An *a priori* sample size estimation was performed using the following sample size calculation formula (68):

$$\begin{array}{l} Sample\;size\;=\;\frac{{Z_{-a/2}}^{2}SD^{2}}{d^{2}} \end{array}$$

Where: *Z*_−*a*/2_ is a standard normal variate (at 5% type 1 error i.e., *P* < 0.05, it is 1.96); *SD* is the standard deviation of the main variable based on previous study; and *d* is the absolute error or precision based on previous study.

The primary outcome of this study is to investigate the evolution of exercise tolerance using the 6-MWT distance. According to Granger et al. (69), a 9.5% decline in the walking distance (i.e., exercise performance) during the 6-MWT test is sufficient to show a clinical decrease in exercise tolerance. Thus, based on the evolution of 6-MWT distances between the first and the second visit in our study, the hypothesis was that cancer patients will reduce, by at least 9.5%, their 6-MWT performance, and thus exhibit signs of exercise intolerance. We also determined the expected baseline 6-MWT results (659 ± 62 m) from the results observed in a healthy subjects group aged 55–75 years old (70), and a 7-m precision was calculated according to a test-retest reliability performed by Demers et al. (67). Using an α level of 0.05 and a power (1-β) of 0.95, the total sample size was calculated as follows:

$$\begin{array}{l} Sample\;size=\frac{1.96^{2}{\left(62\right)}^{2}}{7^{2}}=301 \end{array}$$

Our sample (*n* = 301) will be equally divided into our three groups of interest: 100 lung cancer patients, 100 breast cancer patients, and 100 colorectal cancer patients.

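### The sample-size paragraph claims 95% power for a calculation that has no power term; 301 is a precision figure for one pooled mean, and it does not address change or the comparison by cancer type

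*Protocol article*

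**What the plan says.** The Sample Size section of the protocol article names the evolution of 6-minute walk distance as the primary outcome. It hypothesises a fall of at least 9.5% between the first and second visits. The SD comes from "the expected baseline 6-MWT results (659 ± 62 m) from the results observed in a healthy subjects group" aged 55–75. For the allowable error the article says that "a 7-m precision was calculated according to a test-retest reliability performed by" a cited study. The formula is n = Z²SD²/d², where d is described as an absolute error or precision and Z is 1.96. The calculation is then introduced with "Using an α level of 0.05 and a power (1-β) of 0.95, the total sample size was calculated as follows" and gives 301.

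The article says this total "will be equally divided into our three groups of interest: 100 lung cancer patients, 100 breast cancer patients, and 100 colorectal cancer patients". The Abstract agrees on the split: "The PROTECT-01 cohort study will include 300 patients equally divided between lung, breast and colorectal cancer". The Statistical Analysis section plans a mixed-design ANOVA of three cancer groups by three visits. The Discussion gives the comparison of the three cancers as a main purpose.

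**The concern.** Power is the probability that a stated test detects a stated effect. The printed formula involves no test, no effect and no beta. The result would be 301 whatever power was written beside it, so the claim and the calculation in the same paragraph do not fit together.

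Three further mismatches are visible within the article:

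- The only effect it hypothesises, the 9.5% decline, is not an input.
- The SD describes the spread of one walk among healthy people. The outcome is the change within patients, for which the article gives no SD.
- The total is set for all patients together, while the planned analysis compares three groups of 100.

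A reader who takes 0.95 at face value may attach it to the group × time test and read a non-significant interaction as strong evidence that the cancers do not differ. A reader may likewise carry the ±7 m over to each cancer type, to which the calculation does not apply.

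**Working it through.** **Inputs from the article:** Z = 1.96; SD = 62 m and mean 659 m (healthy subjects, one occasion); d = 7 m; stated power 0.95; hypothesised decline 9.5%; 3 × 100 patients. **Not in the article:** the SD of change and the correlation between visits. Values for these below are assumptions.

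**1. The article's own figure.** 1.96² × 62²/7² = 3.8416 × 3844/49 = 301.4. The 301 reproduces, as a precision calculation for one mean.

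**2. Precision delivered at SD 62 m.**
- Pooled single-visit mean, n = 300: 1.96 × 62/√300 = 7.02 m.
- One group, n = 100: 1.96 × 62/√100 = 12.15 m.
- Difference between two groups of 100: 1.96 × 62 × √(2/100) = 17.19 m.

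**3. Power for the hypothesised decline.** 0.095 × 659 = 62.6 m. Against zero change, power ≈ Φ(62.6/(SD_change/√n) − 1.96).
- n = 100, SD_change 62 m: Φ(10.10 − 1.96), above 0.999.
- n = 100, SD_change 100 m (assumed): Φ(6.26 − 1.96), above 0.999.
- n = 100, SD_change 150 m (assumed): Φ(4.17 − 1.96) = 0.987.

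At SD_change 62 m, 95% power would need (1.960 + 1.645)² × 62²/62.6² = 12.7, or 13 patients. So 301 does not come from this hypothesis.

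**4. Precision for the Visit 1 to Visit 2 change.** With equal variances at both visits, SD_change = 62 × √(2(1 − r)), for an assumed correlation r. The 95% half-widths in metres are:

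| r (assumed) | SD of change | Pooled, n = 300 | Per group, n = 100 | Between two groups |
|---|---|---|---|---|
| 0.85 | 34.0 | 3.8 | 6.7 | 9.4 |
| 0.7 | 48.0 | 5.4 | 9.4 | 13.3 |
| 0.5 | 62.0 | 7.0 | 12.2 | 17.2 |
| 0 | 87.7 | 9.9 | 17.2 | 24.3 |

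The last column is 1.96 × SD_change × √(2/100). The value 0.85 equals the test reproducibility coefficient given under Exercise Tolerance. Nothing in the article says that it holds across eight weeks of treatment.

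A per-group half-width of 7 m needs SD_change ≤ 7 × 10/1.96 = 35.7 m. At SD 62 m this means r ≥ 1 − (35.7/62)²/2 = 0.83.

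**5. If patients vary more than healthy subjects.** With an assumed single-visit SD of 80 to 120 m, the pooled single-visit half-width is 1.96 × SD/√300 = 9.1 to 13.6 m.

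**The case against.** The study is a descriptive cohort, and sizing such a study by precision is legitimate. The arithmetic is right, d is openly called a precision, and ±7 m is what 300 patients give for the quantity calculated. The 0.95 may be the 95% confidence level under the wrong name, although that is inference. All of this stands. It defends the number 301, not the sentence that attributes a power to it.

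A reader might go further and infer that the study is underpowered. If 7 m is treated as the effect to detect, power at SD 62 m is about 0.50 with 301 patients and 0.20 with 100, and 95% would need about 1,020: (1.960 + 1.645)² × 62²/7². The article does not support this reading. It uses 7 m as a precision, and the only effect it hypothesises is the 9.5% decline, for which power against zero change is very high.

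A reader might also infer that ±7 m is not achieved at all. It is achieved for the pooled single-visit mean at SD 62 m, and for the pooled mean change at that SD once the correlation is about 0.5 or more.

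Nor are the group comparisons shown to be uninformative. At an SD of change of 62 m, the between-group difference detectable with 80% power is (1.96 + 0.84) × 62 × √(2/100) = 24.6 m, well below 62.6 m.

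Two smaller matters carry no weight. The gap between 301 and 300 patients moves the half-width by about 0.01 m. An allowance for loss to follow-up may sit in the full protocol.

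**Conclusion.** The concern holds as a misstatement of the basis for the sample size. The power of 0.95 is not a product of the printed calculation and should not stand. What was calculated is a ±7 m interval for one pooled mean, with a healthy-subject, single-visit SD. It does not cover the within-patient change or the group × time comparison.

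At SD 62 m the half-width is ±12.2 m per group and ±17.2 m between two groups, against the quoted 7 m. For the change, the per-group figure runs from 6.7 to 17.2 m as the assumed correlation falls from 0.85 to 0. It would be wider if patients vary more than the healthy reference group.

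These figures rest on normal approximations, full follow-up, equal variances across visits and correlations that the article does not give. They do not show that the sample is too small for the stated hypothesis tested against zero change.

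**What to change.** In the Sample Size section:

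1. Delete the statement of 95% power.
2. Give the size as 300 (3 × 100). Describe it as a precision calculation for the pooled mean distance, with an SD taken from healthy subjects.
3. Add 95% half-widths for the Visit 1 to Visit 2 change, per group and between two groups, over a stated and assumed range of SD of change. An example is 34 to 88 m, from SD 62 m with correlation 0.85 to 0. Include larger values in case the spread in patients is wider.
4. Say that the calculation was not made for the group × time test.

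This rewrites one paragraph. It needs no extra patients and leaves the analysis unchanged. The cost is the loss of the power claim, and the group-level precision is then seen to be wider than 7 m under most of these assumptions.
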